## Abstract

Violence against women and girls is an important global health concern. Numerous health organizations highlight engaging men and boys in preventing violence against women as a potentially impactful public health prevention strategy. Adapted from an international setting for use in the US, “Manhood 2.0” is a “gender transformative” program that involves challenging harmful gender and sexuality norms that foster violence against women while promoting bystander intervention (i.e., giving boys skills to interrupt abusive behaviors they witness among peers) to reduce the perpetration of sexual violence (SV) and adolescent relationship abuse (ARA). Manhood 2.0 is being rigorously evaluated in a community-based cluster-randomized trial in 21 lower resource Pittsburgh neighborhoods with 866 adolescent males ages 13–19. The comparison intervention is a job readiness training program which focuses on the skills needed to prepare youth for entering the workforce, including goal setting, accountability, resume building, and interview preparation. This study will provide urgently needed information about the effectiveness of a gender transformative program, which combines healthy sexuality education, gender norms change, and bystander skills to interrupt peers’ disrespectful and harmful behaviors to reduce SV/ARA perpetration among adolescent males. In this manuscript, we outline the rationale for and evaluation design of Manhood 2.0.

## Introduction

1.

### Background and rationale

1.1.

Sexual violence (SV) and intimate partner violence affect at least one in three women in the world [1] including in the United States [2]. Among adolescents in the US, non-partner SV often co-occurs with adolescent relationship abuse (ARA; physical, sexual, or emotional abuse by a partner) victimization [3], and such experiences are associated with poor health, including suicidality, depression, substance use, unintended pregnancy, and sexually transmitted infections (STIs) [4–13]. Perpetration of SV/ARA is associated with multiple individual and contextual factors, including exposure to adverse childhood experiences, poor conflict resolution and relationship skills, and norms that condone violence perpetration [14]. Prevention entails modifying potential perpetrator behaviors, which in turn requires attention to both individual attitudes and the normative peer context. [14]

This study addresses SV and ARA perpetrated against adolescent females as a gendered problem, based on multiple studies demonstrating the relationship between males’ gender inequitable practice (attitudes and behaviors that degrade women and promote ‘rigid masculinity’) and SV/ARA perpetration by adolescent males [15–27]. Gender inequitable practice is associated with poor health outcomes for men (including HIV infection) and increased violence victimization and poor outcomes for women [22,28–30]. Health interventions that focus on promoting gender equity demonstrably reduce violence and substance use, increase condom use, decrease transactional sex, and increase communication between couples. [31–39]

As SV/ARA perpetration often emerges in the context of male peers who demonstrate negative attitudes toward females, endorse bias-based prejudices regarding homosexuality and condone abuse perpetration [40–47], prevention requires addressing potential perpetrator attitudes and behaviors as well as the gendered peer environment in which they are embedded. Perceived peer tolerance for SV/ARA may promote individual likelihood of these behaviors, and may reduce comfort and ability to intervene when faced with negative behaviors among peers, contributing to a social climate that enables such behavior [42]. Many violence prevention programs focused on social norms change employ a bystander behavior approach, in which individuals are taught skills to respond with active intervention in SV/ARA rather than with apathy or tolerance [48,49]. This study draws on building bystander intervention skills combined with evidence from international settings that demonstrated the effectiveness of encouraging critical analysis of gender norms, challenging homophobia and gender-based harassment, and building skills both to critically question harmful masculine norms and to employ more equitable behaviors.

The literature on adolescent sexual health promotion also underscores the need for skills building that includes an emphasis on respect, communication about pregnancy and STI and HIV/AIDS prevention, condom negotiation, sexual consent, and learning about reproductive and sexual coercion [50–52]. The most effective sexual health interventions also address gender and power [53]. Integration of open, in-depth discussions about respectful sexual behaviors that also address homophobia and rigid masculinity norms may simultaneously reduce SV/ARA perpetration and improve sexual health. In international settings, sexual health promotion programs that incorporate changing cultural norms around masculinity (i.e., “gender transformative” programs), focused on older adolescents and young adults, have demonstrated significant positive shifts in gender attitudes as well as increased use of condoms and decreased reporting of men’s use of violence towards an intimate partner [29,32,43,54,55]. This is the first study to test the effectiveness of a community-based program for adolescent males that combines healthy sexuality skills, gender norms change, and bystander skills to interrupt peers’ disrespectful and harmful behaviors to prevent SV/ARA perpetration among adolescent males.

## Methods

2.

### Adaptation of an international gender transformative curriculum

2.1.

The intervention to be tested in this study – titled “Manhood 2.0” – is the first U.S. adaptation of the well-established Program Η (“H” stands for “homem” meaning “man” in Portuguese), a gender-transformative curriculum tailored for young men (https://promundoglobal.org/programs/program-h/). Developed in Brazil by Promundo (a global gender equality and violence prevention organization) and their partners in global health, Program H is an integrated curriculum and community outreach model (see: Fig. 1) to engage adolescent and adult men in health promotion, gender equality, and gender-based violence prevention that has been implemented in 29 countries. The evaluation studies conducted to date in global settings have found promising changes in attitudes that support gender-based violence and in some settings to lead to reductions in young and adult men’s reported use of violence. Based on these results, Program H has been acknowledged by PAHO, UNICEF, UNFPA, UNDP, the World Bank and the Brazilian Ministry of External Relations as a best practice in promoting gender equality.

Program H was identified by the PI as a promising program to adapt for efforts to prevent SV/ARA in the U.S. The key adaptations of Program H to create Manhood 2.0 include additional discussions of social media use, internet pornography, deeper explorations of inter-sectionality using visual art (examining the unique experiences of racism and marginalization experienced by young African-American men in the United States, examining white privilege, male privilege), female-controlled contraception (including long-acting reversible contraception [LARCs]), and practicing bystander intervention skills.

#### Theoretical and empirical basis for the intervention

2.1.1.

There are several theoretical and empirical bases for the Manhood 2.0 intervention on SV/ARA perpetration, including:

##### A program that integrates gender norms change, education about healthy sexuality, and promotion of positive bystander intervention behaviors is likely to address several modifiable risk factors related to SV/ARA perpetration.

2.1.1.1.

From the evidence emerging from the epidemiology of SV/ARA and studies of current SV/ARA prevention programs, SV/ARA perpetration prevention requires integration of several core intervention components that are theoretically and empirically grounded [14,56–59]. Consistent with Social Norms Theory [42,60] and Theory of Reasoned Action combined with the Theory of Gender and Power [61], the Manhood 2.0 program trains prevention educators to facilitate discussions with adolescent males that: 1) promote gender equitable attitudes, 2) encourages adolescent males to reflect on how gender norms and power dynamics influence behaviors related to violence and sexual behaviors 3) educates adolescent males in healthy sexuality skills to increase sexual communication, consent, and recognition of sexual coercion, and 3) encourages positive bystander intervention when witnessing violent and inequitable behaviors among peers. By encouraging critical reflection and challenging harmful and violent and inequitable behaviors in the context of heterosexual relationships, this intervention aims to address the parts of youth socialization that endorse norms, attitudes, and behaviors that facilitate violence and unhealthy behaviors. In doing so, the program aims to promote critical transformation of these norms towards gender equity.

Shifting gender norms, reducing homophobic attitudes, educating about sexuality and sexual consent, and developing positive bystander intervention skills influence not only individual attitudes and behaviors, but also the peer and social context in which these youth are embedded. A program that integrates these areas (gender norms change around rigid masculinities, reflection on power dynamics, education about healthy sexuality, and positive bystander intervention) has not yet been rigorously evaluated in the U.S.

##### Community-based SV/ARA prevention programs which are flexible around how and when curriculum is delivered and which do not rely on school district approvals for implementation are needed.

2.1.1.2.

Some school-based teen pregnancy and HIV prevention education efforts in the U.S. have emphasized abstinence and facts about contraception, condom use, and STIs [62,63]. Simultaneously, few pregnancy and HIV prevention programs address SV/ARA, sexual consent, condom negotiation, and gender norms. Whereas school-based classroom instruction is often broken into one to two hour segments [64–66], implementation in more informal community settings allows for lengthier and deeper conversations about sexuality and violence over the course of several days that is likely to increase interactions, questions, and personal reflections among youth [67].

##### Youth development-focused community programs engage adolescent males living in socially disadvantaged neighborhoods through a range of modalities including community-based athletics, after school programs, employment programs, and truancy programs.

2.1.1.3.

The population for this study is adolescent males ages 13–19 (primary focus is high school-age youth) living in the socially disadvantaged, primarily African American neighborhoods of Pittsburgh. The rationale for focusing on primarily African American youth in lower resource neighborhoods is two-fold.

First, racial/ethnic disparities in health in Pittsburgh are stark. The county has the second highest rate of teen birth to African American adolescent females in the state [68], a prevalence of STIs among African American adolescent females that is twice the national average [69,70], while firearm-related injuries and death disproportionately impact both African American males and females [71,72]. Exposures to community violence, as well as the social context for unintended pregnancy and STIs, are closely linked to increased vulnerabilities for sexual violence [45,47,73]. Our research and others have underscored the multiple ways that poverty increases these vulnerabilities including through economic dependency, sexual exploitation, drug trade, survival sex, and gang affiliation [73–76]. Prevention efforts in communities with high prevalence of poverty, violence, and poor health outcomes are needed, informed by the social and economic justice frameworks that are the foundational principles among the community partners and stakeholders participating in this project.

Second, the prevention educators working within these youth-serving agencies are from the communities in which they are working, and are highly trusted and respected. Many also oversee informal athletic programs, after-school programs, and school-based prevention education, allowing them to work across multiple social settings. Thus, these community programs and facilitators are well positioned to recruit and retain a heterogeneous sample of adolescent males and their peers through these existing social networks. In line with core principles for prevention programs, as recommended by Nation [67], these prevention educators are likely to be able to connect with youth in meaningful and sustainable ways.

##### Sustainable, scalable community programs to prevent SV are needed.

2.1.1.4.

We have too few evidence-based SV/ARA prevention programs in the U.S. focused on adolescents that can be delivered by community members/youth agency staff without extensive training [64–66]. We have only one evidence-based SV/ARA prevention program focused on adolescent males and that is in the context of school-based athletics only [37,77]. No evidence-based SV/ARA programs for youth take place outside of the classroom or school-based athletics setting. This study will advance scientific knowledge about SV/ARA perpetration prevention (with an emphasis on primary prevention) and address these gaps in the existing evidence base. This research will provide urgently needed information about the relevance of an innovative community-based SV/ARA prevention program adapted from international prevention efforts for implementation with adolescent males in community-based settings.

The intervention involves an 18 h curriculum divided into six 3h sessions delivered once or twice a week (generally over 3 to 6 week time period). This design builds on primary prevention principles that emphasize a comprehensive, theory-driven approach, sociocultural relevance, well-trained staff, opportunity for building positive relationships with youth, sufficient dosage (through repeated exposure to content), and youth participation balanced with feasibility and cost of implementation approaches [67,78]. Program implementation relies on the youth development infrastructure and community-based networks already in place at participating YMCAs, Urban League, and other youth development organizations in Pittsburgh, including the ability to reach diverse adolescent males with the assistance of other youth-serving community agencies including schools, libraries, and churches. Multiple stakeholders at the local, regional, national, and global level are involved to ensure the program is relevant, easy to implement, and replicable, thus if found to be effective, could be widely disseminated as a promising prevention program.

### Objectives

2.2.

This cluster-randomized community-based intervention will examine the effectiveness of a program for the primary prevention of SV/ARA titled “Manhood 2.0.” This program seeks to alter gender norms that foster SV/ARA perpetration, while promoting bystander intervention (i.e., giving boys skills to interrupt disrespectful and abusive behaviors they witness among peers) and respectful sexual behaviors, to reduce SV/ARA perpetration.

The primary objective of this study is to test the effectiveness of Manhood 2.0 compared to a job skills development curriculum on 1) reductions in self-reported perpetration of SV and ARA (*Primary Outcome)* toward females and 2) increased positive bystander intervention behaviors (*Secondary outcome*). Intermediate outcomes include increased condom self-efficacy; contraceptive use attitudes; increased recognition of abusive behaviors; increased gender-equitable attitudes; and increased intentions to intervene with peers.

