#### SV/ARA perpetration

2.10.1.

At baseline and T3 (9 months post-intervention), participants report whether they perpetrated the following SV or ARA behaviors in the last 9 months. The primary outcome measure for the study is any report of SV or ARA perpetration, i.e., yes to any of the following items.

The following two constructs focus on ARA behaviors against a dating partner. “Any ARA perpetration” is measured as a yes to any of these 13 items.

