#### Dating abuse

2.10.3.

A ten-item scale, developed for use with high school-aged students, is used to assess whether the participant perpetrated any abuse against a dating partner [37]. Examples include “convinced them to have sex, after they said no a few times” and “told them not to talk to others or told them who they could hang out with. ” A positive response to any of these items is counted as any ARA perpetration.

“Any SV perpetration” is measured as yes to any of the sexual relationship violence and dating abuse items above as well as yes to any of the behaviors below.

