#### Sexual harassment

2.10.7.

Five items assess the frequency with which a participant has engaged in sexual harassment against someone from “making unwanted sexual comments” to “touching or grabbing them in a sexual way.” [82,83] Any endorsement of these behaviors is coded as yes for sexual harassment.

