Missing data were minimized as much as possible by keeping the surveys as short as possible to reduce survey burden, encouraging youth to be as complete and honest as possible by ensuring anonymity of the surveys, and working assiduously with community partners to ensure that youth stay engaged and can be tracked to complete follow up surveys. Mechanisms for missing data will be investigated by comparing important covariates between youth with and without missing data at each time point. We will characterize these mechanisms as 1) missing completely at random (MCAR), 2) missing at random (MAR), or 3) not missing at random (NMAR). If the nature of our missing data is ignorable (either MCAR or MAR), our primary analysis will be sufficient given that it is a likelihood-based approach to handling missing data. Additionally, we will conduct various sensitivity analyses such as multiple imputation via chained equations (MICE) and complete-case analyses. If our missing data is non-ignorable (MCAR), we will investigate other methods such as joint or shared parameter models.

The primary outcome for this study is reductions in self-reported perpetration of SV and ARA at Time 3, compared to controls. We will examine whether Manhood 2.0 results in improvements in the primary outcome assessed at 9 months after end of program (Time 3) compared to controls. Generalized linear mixed models (GzLMM) will be used and will include variables for baseline SV/ARA perpetration, treatment group, and random effects for cluster. For the primary outcome and other binary outcomes, the GzLMMs will be fit using a logit link; for all other continuous outcomes, an identity link function will be used.

For positive bystander intervention and the remaining secondary outcomes, the models will include variables for the secondary outcome at baseline, treatment group, and random effects for cluster. This will allow us to assess the effect of the study arm after accounting for clustering within neighborhoods. As an exploratory analysis, all three time points will be included in a single generalized linear mixed model to quantify the long-term trajectories of each of the secondary outcomes.

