	Primary Outcome: Any Sexual Violence/Adolescent Relationship Abuse Perpetration (comparing differences between intervention and control at Time 3)					
Physical/sexual IPV [79]	Yes/no to each Modeled as yes to any lifetime (baseline only) and yes to any past 9 months	X			X	*Have YOU done any of the following to someone you were in a relationship with (like he or she was your partner/girlfriend/boyfriend, you were dating or going out with, them) or hooking up with:* 1. …[ever/in the past 9 months] hit, pushed, slapped, choked or otherwise physically hurt someone you were going out with or hooking up with? (include such things as hitting, slamming into something, or injuring with an object or weapon.) 2. …[ever/in the past 9 months] used physical force or threats to make someone you were going out with or hooking up with have sex (vaginal, oral, or anal sex) when they didn’t want to? 3. … [ever/in the past 9 months] had sex with someone you were going out with or hooking up with when they didn’t want to or because you made them feel like they didn’t have a choice (even though you did not use physical force or threats)?
Dating abuse [37]	Baseline - No, I have never done this to someone I was in a relationship with - Yes, I have done this in the past 9 months - Yes, I have done this, but not in the past 9 months T3: Yes/no Modeled as summary score for lifetime (baseline only) and past 9 months	X			X	*Have YOU done any of the following to someone you were going out with (like he or she was your partner/girlfriend/boyfriend, you were dating them) or hooking up with:* 1. Spread rumors about their sexual reputation, like telling people they’re ‘easy’. 2. Convinced them to have sex, after they had said no a few times. 3. Made them have sex when they didn’t want to. 4. Physically hurt them (like shoving, grabbing, slapping, punching, choking). 5. Threatened to hurt them if they didn’t do what you wanted them to do. 6. Yelled at them or destroyed something that belonged to them. 7. Called them names, like ugly or stupid. 8. Told them not to talk to others or told them who they could hang out with. 9. Showed friends or posted pictures of them naked or doing something sexual. 10. Talked about what you and your partner do sexually with your friends or peers.

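### The primary objective is perpetration toward females, but no printed primary item separates victims by sex, and the any-SV definition takes in non-sexual items

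*Protocol article*

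**What the plan says.** **Target.** Section 2.2 gives the primary objective as reductions in self-reported perpetration of SV and ARA "toward females and 2) increased positive bystander intervention behaviors". Section 1.1 has the same focus: "This study addresses SV and ARA perpetrated against adolescent females as a gendered problem".

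**Outcome.** Section 2.10.1 has no such limit: "The primary outcome measure for the study is any report of SV or ARA perpetration", met by a yes to any listed item. Section 2.18 says "The primary outcome for this study is reductions in self-reported perpetration of SV and ARA at Time 3, compared to controls". The Discussion also leaves out victim sex.

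**Items.** In Table 2 the partner items describe the other person with "like he or she was your partner/girlfriend/boyfriend, you were dating or going out with". The remaining primary items ask about acts against someone, anyone or people not dated.

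**Any SV.** Section 2.10.3 says that any SV perpetration "is measured as yes to any of the sexual relationship violence and dating abuse items above", together with the behaviours listed after it.

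**Component coding.** For dating abuse, section 2.10.3 counts a positive answer to any item, while Table 2 has "Modeled as summary score for lifetime (baseline only) and past 9 months". For sexual harassment, section 2.10.7 has "Any endorsement of these behaviors is coded as yes for sexual harassment", while Table 2 again has a summary score.

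**The concern.** The objective names a narrower target than the instrument measures. Acts against males count as events and, on the printed items, cannot be separated out. A positive result written up against section 2.2 would be reported as less violence toward females, which was not measured separately. If the programme changes behaviour mainly toward females, acts against males would also dilute the contrast.

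The any-SV definition is a second problem. If it takes in name-calling, yelling and controlling contacts, it is hardly distinguishable from the combined outcome, and any SV result drawn from it would not be specifically about sexual violence. The boundary already matters in section 2.12, which names the primary outcome as any SV/ARA but bases its power on a 20% SV perpetration rate.

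The double coding of two components looked as if it might leave the primary outcome with two definitions. Step 3 of the working shows that it does not.

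**Working it through.** **1. Victim sex, item by item (Table 2)**

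| Component | Items | Victim as worded | Limited to females |
|---|---|---|---|
| Physical/sexual IPV | 3 | partner, he or she | 0 |
| Dating abuse | 10 | partner, he or she | 0 |
| Non-partner SV | 2 | people not dated, including strangers, friends, family | 0 |
| Sexual harassment | 5 | someone | 0 |
| Cyber sexual abuse | 3 | someone | 0 |
| Incapacitated sex | 1 | someone | 0 |
| Alcohol or drugs on purpose | 1 | someone | 0 |
| **Total** | **25** | | **0** |

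The partner items number 3 + 10 = 13 and the others 2 + 5 + 3 + 1 + 1 = 12. No printed follow-up question asks the victim's sex. By contrast, all nine bystander items in the same table name a girl, a girlfriend, or women and girls, so the instrument does specify female targets elsewhere.

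**2. What any SV covers (section 2.10.3)**

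- As written: IPV items 2 and 3 (2), all dating-abuse items (10) and the later behaviours (12). 2 + 10 + 12 = 24 of 25.
- The item left out is IPV item 1, physically hurting a partner. Dating-abuse item 4 asks nearly the same thing, so any SV and any SV/ARA differ only for a boy who says yes to IPV item 1 and no to everything else.
- Dating-abuse items 4 to 8 (physical hurt, threats, yelling or destroying property, name-calling, controlling contacts) have no sexual content: 5 of 10.
- If the word sexual is read as covering dating abuse too, items 2, 3 and 9 clearly qualify, while items 1 and 10 are open to judgement. The count is then 2 + 3 + 12 = 17 up to 2 + 5 + 12 = 19. The article does not say which reading applies or which items qualify.

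**3. Does the double coding change the primary outcome?**

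A summary score counts endorsed items, so a score above 0 is the same event as a yes to any item. Section 2.10.1 fixes the composite as yes to any, and section 2.18 fits it with a logit link. The composite is therefore the same under either label. Only analyses of the two components (2 of 7) are affected, because section 2.18 assigns a logit link to binary outcomes and an identity link to continuous ones.

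**4. Possible dilution (illustration only)**

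The plan's figure comes first. Section 2.12 gives a 20% control rate and an 8.3-point difference: 0.083 / 0.20 = 0.415, which matches its 42% relative decrease. With 80% retention there are 866 × 0.8 / 2 = 346.4 per arm and 866 × 0.8 / 21 = 33.0 per cluster. The design effect is 1 + (33.0 − 1) × 0.01 = 1.32, and the effective n is 346.4 / 1.32 = 262.4 per arm. A two-sided 5% z test of 20% against 11.7% then has 74% power, not the stated 80%. Ignoring attrition (n = 866, design effect 1.40) gives 80.8%. That discrepancy is a separate matter; 74% serves here only as the starting value.

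Let q be the share of perpetrators whose victims were all male. Assume the programme does not affect them and that perpetration among the rest falls by 41.5%. The difference in the composite is 0.20 × (1 − q) × 0.415.

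| q (assumed) | Difference | Power |
|---|---|---|
| 0% | 8.3 points | 74% |
| 5% | 7.9 points | 69% |
| 10% | 7.5 points | 64% |
| 20% | 6.6 points | 53% |
| 30% | 5.8 points | 42% |

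If the programme reduces acts against males in the same proportion, there is no dilution.

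**The case against.** The strongest reply is that the restriction to females appears in one sentence of the objectives and in no endpoint definition. Sections 2.10.1, 2.12 and 2.18, the heading in Table 2 and the Discussion all give any SV/ARA perpetration. That outcome is coherent and testable, and counting victims of any sex does not bias the randomised comparison. This stands. A reader might infer that the trial cannot answer its primary question at all. The documents do not support that; they support only a limit on what may be concluded about females.

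Table 2 may also not be the whole survey. Section 2.18 plans moderators, such as sexual risk and connectedness, that have no item in the table, so an unprinted question on partner or victim sex is possible. This stands too, and is why the point is confined to the items shown.

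On any SV, the reply is that it is neither the primary nor a listed secondary outcome, that the article describes no separate SV analysis, and that the sentence can be read as limited to sexual dating-abuse items. The first two parts lower the stakes: with no item frequencies and no planned analysis, nothing shows that non-sexual items would drive an SV result. The third does not rescue the definition, because no list of qualifying items is given.

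Finally, the size of any dilution is unknown. That is correct, and the figures for q are assumptions.

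**Conclusion.** The point holds in limited form. None of the 25 printed primary items is restricted to female victims or records victim sex, so on those items the trial can estimate an effect on any SV/ARA perpetration but not on perpetration toward females. The objective and the measure disagree, and a conclusion worded from the objective would go beyond the data.

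The any-SV definition, read as written, covers 24 of 25 items, including five non-sexual ones, and so does not define a distinct outcome.

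A reader might also infer from the summary-score labels that the primary outcome has two definitions. It has one, and the labels matter only for component results.

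The effect on power cannot be fixed from the documents. The range of 8.3 down to 5.8 points for q from 0% to 30% rests on an assumed share, on no programme effect on boys with only male victims, and on treating each other perpetrator as wholly stopping or continuing. The counts in steps 1 and 2 need none of these assumptions.

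**What to change.** 1. **Objective and conclusion.** Remove the restriction to females from section 2.2, or keep the gendered rationale but state that victim sex is not separated and that conclusions concern perpetration against any partner or non-partner. If the full survey does record victim sex, cite the item and define the female-directed outcome from it.
2. **Any SV.** Replace the sentence in section 2.10.3 with an item list fixed before analysis: IPV items 2 and 3; dating-abuse items 2, 3 and 9, with a stated decision on items 1 and 10; and the non-partner, harassment, cyber, incapacitated-sex and alcohol/drug items.
3. **Table 2 (minor).** Align the dating-abuse and sexual-harassment entries with the yes-to-any coding in sections 2.10.3 and 2.10.7, or label the scores as additional component analyses.

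The cost is wording and one derived-variable definition. No new data are needed, and the primary composite and its model stay as they are.
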